## Variables measurement

4

Socio-demographic variables will be collected from patients at baseline. Clinical reagent testing and questionnaires will be completed at baseline as well as at 3 and 6 months of follow-up, with data collection times shown in Table 2.

**Table 2 tab2:** Data collection components and collection timeline.

Data collection component		Timepoint		
		0 M	3 M	6 M
Sociodemographic variables	Age, gender, educational level, economic status, living conditions ; Duration of illness, number of medications taken, history of adverse drug reactions, source of drug information	√		
Clinical Health Indicators	BP, LDL-C, HbA1c, FPG, NIHSS	√	√	√
Medication adherence	Questionnaire: ARMS-7	√	√	√
Quality of life	Questionnaire: EuroQol-5 Dimensions 5 Levels(EQ-5D-5L)	√	√	√
Medication Literacy	ML-scale	√	√	√
Medication administration accuracy rate	Questionnaire: Medication Error Survey Form	√	√	√
Self-efficacy for Appropriate Medication	Questionnaire: Self-efficacy for Appropriate Medication Use Scale, SEAMS	√	√	√
Depression and anxiety	Questionnaire: Simplified version of the Anxiety Depression Scale (PHQ-4)	√	√	√
Readmission rate	Readmission rate			√

## Questionnaires

5

### Refill or medication adherence scale (ARMS-7)

5.1

ARMS-7was used to assess the level of medication adherence in patients. The scale was developed by Kripalani et al. (67) and consists of seven entries divided into two dimensions: medication adherence (entries 1 to 4) and refill behavior (entries 5 to 7). Each entry is scored on a 4-point Likert scale, where 1 represents ‘not at all’ and 4 represents ‘always’, with a total score ranging from 7 to 28. It is important to note that the 7th entry is reverse scored, i.e., 1 for ‘always’ and 4 for ‘not at all’. Higher total scores indicate poorer medication adherence, and the ARMS-7 scale has high reliability and validity, with item correlation coefficients ranging from 0.35 to 0.58 and Cronbach’s alpha coefficients of 0.75, which suggests that the scale has good internal consistency (64).

### Simplified version of the medication literacy scale (ML-scale)

5.2

A simplified version of the Medication Literacy Scale (ML-Scale) previously validated by our group was used to assess the level of drug literacy in patients (68). The scale was previously validated by our group and was highly compatible with the present study. The reliability of the scale was confirmed by Cronbach’s alpha coefficient (0.799) and Omega coefficient (0.785), indicating good internal consistency of the assessment tool. The results of the validation factor analysis showed that the average variance extracted (AVE) ranged from 0.718 to 0.830 and the composite reliability (CR) ranged from 0.835 to 0.830, which are data that indicate that the convergent validity of the scale is more satisfactory. Structural validity was supported by the following metrics: chi-square to degrees of freedom ratio (/df) of 53.877, goodness-of-fit index (GFI) of 0.996, canonical fit index (NFI) of 0.997, relative fit index (RFI) of 0.992, and root-mean-square error approximation (RMSEA) of 0.042. The scales were scored on a five-point Likert scale, with a total score range from 0 to 30, with higher scores indicating a higher level of drug literacy in the patient.。.

### Medication error questionnaire

5.3

In this study, the Medication Error Questionnaire was used to assess the errors that patients may have made during the actual administration of medication. The questionnaire was designed by Huiling (69) and contained 10 entries covering various aspects of medication errors. Each entry was also scored on a 4-point scale with a total score ranging from 10 to 40, with higher scores indicating a lower incidence of medication errors. The Cronbach’s alpha coefficient was 0.852, indicating good internal consistency of the scale.

### Self-efficacy for appropriate medication use scale (SEAMS)

5.4

This scale was developed by Risser et al. (70) in 2007 based on the self-efficacy theory to assess patients’ self-efficacy in appropriate medication use. The scale consists of two dimensions, confidence in adhering to medication in uncertain situations and difficult situations, and consists of a total of 13 entries. A Likert 3-point scale was used, with scores ranging from 1 (no confidence) to 3 (very confident) and a total score ranging from 13 to 39, with higher scores indicating higher levels of self-efficacy in rational medication use among the subjects. The scale was rigorously translated by Dong (71) based on Brislin’s translation principles and was investigated in 480 stroke patients to test its reliability and validity. The retest reliability of the Chinese version of the SEAMS was 0.932, and the Cronbach’s alpha coefficient for the whole scale was 0.934. Two cofactors were extracted by exploratory factor analysis, with a cumulative variance contribution of 55.821%, and the factor loadings of all the entries on their communal factors exceeded 0.4. The content validity index at the scale level (CVI) was 0.913, indicating that the scale is applicable and has good applicability for the evaluation of medication taking in stroke patients.

### Quality of life EQ-5D-5L (EuroQol-5 dimensions 5 levels)

5.5

The quality of life of patients was assessed using the EQ-5D-5L, an improved version of the EQ-5D scale, which adds five levels to the original five dimensions (72, 73), namely, ‘no difficulty’, ‘minor difficulty’, ‘moderate difficulty’, ‘major difficulty’ and ‘complete difficulty’. ‘minor difficulty’, ‘moderate difficulty’, ‘major difficulty’ and ‘total difficulty’. This enables a more detailed assessment of health status. Compared to the original EQ-5D (i.e., EQ-5D-3L), the EQ-5D-5L maintains consistency in dimensional and hierarchical structure, but raises the number of ratings for each dimension from three to five. The five dimensions of the EQ-5D-5L encompass: mobility, self-care, activities of daily living, pain/activities, and pain/tremor. Activities, Pain/Discomfort, and Anxiety/Depression. Individuals select the appropriate level on each dimension based on their condition, creating a five-dimensional description of health status. In addition, the EQ-5D-5L includes a Visual Analog Scale (VAS) that allows individuals to subjectively rate their current state of well-being on a scale of 0 to 100 based on their personal feelings. This score provides a continuous variable to quantify an individual’s overall quality of life.

### Ultra brief depression and anxiety screening scale (patient health questionnaire-4, PHQ-4)

5.6

Developed by Spitzer et al. (74) for rapid screening of patients for symptoms of depression and anxiety. The scale consists of four questions dealing with symptoms such as lack of interest in daily activities, feelings of restlessness, worry and irritability, and low mood. The scale is rated on a scale of 0 to 2, with a total score ranging from 0 to 8. Based on the total score, symptoms can be categorised as normal, mild, moderate and severe. The Cronbach’s alpha coefficient for the PHQ-4 is 0.833, indicating high internal consistency of the scale (75).

### The national institutes of health stroke scale(NIH stroke scale, NIHSS)

5.7

The NIHSS scale was developed by the National Institutes of Health in 1989 to objectively and quantitatively assess neurological deficits in stroke patients through standardised examination items (76). Due to its convenience, reliability, effectiveness and comprehensive nature, it has become an indispensable tool in standardised stroke management and clinical research. The scale comprises 11 items with a total score range of 0–42 points, where a higher score indicates more severe neurological impairment. All assessments are conducted by trained neurologists to ensure consistency and accuracy in evaluation.

### Indicators of clinical health status

5.8

To evaluate the clinical health status of patients, we collected key biochemical and physiological indicators, including blood pressure, HbA1c, FPG, and LDL-C. BP was measured by neurology nurses upon hospital admission and at discharge. The target BP for control was set at <140/90 mmHg, with an ideal range of 120–130/70–80 mmHg; for frail older adults, this target was relaxed to <150/90 mmHg. The target level for LDL-C was <3.36 mmol/L. For glycemic control, HbA1c was used to assess long-term status in diabetic patients, with a target of <7.0%. An HbA1c level of ≥6.5% was used as a diagnostic criterion for diabetes and as a threshold for subgroup analysis. FPG, measured after at least 8 h of fasting, served as an indicator of basal glucose regulation. An FPG level between 6.1–6.9 mmol/L defined impaired fasting glucose (prediabetes) and was also used as a criterion for subsequent subgroup analysis.

### Readmission rate

5.9

Readmission rate was defined as any unscheduled admission to our hospital within 90 days of the index stroke discharge. To provide a more nuanced understanding of post-discharge outcomes, all readmissions were systematically reviewed and classified into the following predefined categories: Stroke Recurrence: Defined as a new acute neurological deficit, confirmed by neuroimaging (CT or MRI) to be a new ischemic or hemorrhagic lesion, and clinically diagnosed by a neurologist. Other Neurological Complications: Readmissions for direct sequelae of the index stroke, such as post-stroke seizures, symptomatic hydrocephalus, or progressive cerebral edema, that were not classified as a new stroke event. Cardiovascular Events: Readmissions for acute myocardial infarction, unstable angina, heart failure, or arrhythmias. Other Stroke-Related Medical Issues: Readmissions for conditions directly related to stroke management or complications, such as uncontrolled hypertension or hyperglycemia requiring hospitalization, urinary tract infection, or pneumonia. Unrelated Causes: Readmissions for reasons clearly unrelated to the stroke or its management (e.g., orthopedic injury, elective surgery). The primary outcome was the 90-day all-cause readmission rate, calculated as the total number of patients readmitted for any reason divided by the total number of discharged patients. Secondary outcomes included the readmission rates for each specific category listed above, particularly the rate of stroke recurrence.

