**Figure 1 fig1:**
[figure not shown]
PMT integration theory diagram.

This study aims to improve the secondary prevention medication adherence of IS patients through the intervention model of PMT combined with drug literacy education. The specific objectives are as follows:

To construct a secondary prevention medication adherence intervention programme for IS patients based on the PMT and drug literacy model, and to validate its effectiveness in improving medication adherence, self-efficacy for medication administration, drug literacy and clinical indicators in IS patients.Evaluate the effectiveness of the AI-HEALS in improving the self-efficacy of health behaviors, quality of life and psychological status of IS patients, and track the reduction in the risk of relapse and readmission.

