## Outcomes

3

Primary Outcome: Change in medication adherence from baseline and at 3 and 6 months of follow-up.

Secondary outcomes:

Changes in medication self-behavior: medication literacy levels, correct medication taking, self-efficacy for rational medication use.Social cognitive and psychological: quality of life, depression, anxiety.Clinical health indicators: blood pressure (BP), low-density lipoprotein (LDL-C) level, glycated Hemoglobin (HbA1c), fasting plasma glucose (FPG), readmission rate.

The corresponding study questionnaires completed by all patients at baseline and follow-up were hosted on a web-based platform (Questionnaire Star). The questionnaires were distributed by the researchers through Questionnaire Star, and patients were instructed to complete them by the researchers either face-to-face (during hospitalisation) or by telephone (after discharge). Patient demographic information was collected through the case system and self-designed questionnaires.

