### Safety

6.10

All serious adverse events (SAEs) and adverse events (AEs) reported by patients or detected by investigators during the study will be recorded and monitored. All SAEs and AEs must be reported to the Principal Study Leader within 24 h of their occurrence and notified to the Monitor and Ethics Committee in accordance with established procedures. The study leader will be responsible for ensuring that all SAEs and AEs are fully documented and that appropriate measures are taken to protect patient safety and rights. Given that digital interventions may present unique challenges, we systematically monitored unintended consequences at the non-clinical level, including: difficulties or frustrations encountered when using the AI-HEALS platform (such as navigation issues, slow loading times, or unclear operational guidance); increased anxiety, stress, or feelings of being overwhelmed stemming from the educational content or the technical use itself; any evidence suggesting patients misunderstood educational information or used the system in unintended ways, which could lead to confusion or erroneous health behaviors. To capture these effects, research assistants proactively telephoned intervention group participants weekly to enquire about any technical difficulties or negative emotions they might have encountered. Participants were encouraged to report any adverse experiences via the research helpline at any time. All reported unintended consequences were documented, with the research team conducting weekly reviews to identify patterns and implement timely solutions. This enabled the provision of additional technical support to patients or clarification of educational content.

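### The readmission definition contradicts itself on scheduled admissions and counts only the study hospital, so the rate is ambiguous and records events elsewhere as non-events

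*Protocol article*

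**What the plan says.** All of the following is in the protocol article.

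- **Definition (section 5.9, Readmission rate).** "Readmission rate was defined as any unscheduled admission to our hospital within 90 days of the index stroke discharge". This fixes the type of admission, the place and the window.
- **Categories (section 5.9).** The last of the five categories is described as "Readmissions for reasons clearly unrelated to the stroke or its management (e.g., orthopedic injury, elective surgery").
- **Rate (section 5.9).** It is "calculated as the total number of patients readmitted for any reason divided by the total number of discharged patients".
- **Status.** Section 5.9 says "The primary outcome was the 90-day all-cause readmission rate". Section 3 (Outcomes) names medication adherence as primary and puts readmission at the end of the secondary clinical indicators: "glycated Hemoglobin (HbA1c), fasting plasma glucose (FPG), readmission rate".
- **Timing (section 4).** "Clinical reagent testing and questionnaires will be completed at baseline as well as at 3 and 6 months of follow-up". Table 2 ticks readmission at 6 months only.
- **Objective (end of section 1).** The trial is to "track the reduction in the risk of relapse and readmission", with no time limit given.
- **Contact by arm.** The intervention arm has daily messages for 3 months after discharge (section 2.5). Under section 6.10, "research assistants proactively telephoned intervention group participants weekly to enquire about any technical difficulties or negative emotions they might have encountered".

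**The concern.** Three parts of section 5.9 disagree on whether a planned admission is an event. The opening sentence excludes it, while the category list and the numerator include it. Two analysts working from the same records could report different rates, and each could point to the text.

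The restriction to one hospital is a separate problem. A patient with a recurrent stroke admitted elsewhere enters the denominator as not readmitted. That value is recorded, not missing, so the multiple imputation in section 5.10 cannot recover it. Stroke recurrence is defined only as a category of these readmissions and has the same gap, although tracking relapse is an objective of the trial.

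The window and the status of the outcome are also left unreconciled with Table 2 and section 3.

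**Working it through.** The plan gives no readmission rate, expected effect or power, so there is no figure of its own to reproduce. The passages can be set side by side, and the consequence shown on assumed values.

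**Inputs.** From the documents: 40 patients per arm (section 2.4), a 90-day window, the study hospital only. Assumed: true 90-day rate p of 10% to 20%; capture c, the share of readmissions that come to the study hospital, of 50% to 90%; elective admissions in 0% to 5% of patients.

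**1. Does a scheduled admission count?** Take a patient whose only admission within 90 days is for elective surgery at the study hospital.

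| Part of section 5.9 | Counted? |
|---|---|
| Definition (unscheduled only) | No |
| Category of unrelated causes | Yes |
| Numerator (any reason) | Yes |

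With p = 15% and c = 70%, unscheduled admissions alone give 0.15 × 0.70 = 10.5%. Adding elective admissions in a further 2% or 5% of patients, assumed to be different people, gives 12.5% or 15.5%. This part of the problem raises the count.

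**2. Events elsewhere.** Observed rate = p × c, and expected events per arm = 40 × p × c.

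| True rate | True events per 40 | Seen at c = 90% | Seen at c = 70% | Seen at c = 50% |
|---|---|---|---|---|
| 10% | 4.0 | 3.6 | 2.8 | 2.0 |
| 15% | 6.0 | 5.4 | 4.2 | 3.0 |
| 20% | 8.0 | 7.2 | 5.6 | 4.0 |

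**3. Equal capture in both arms.** The risk ratio is (p₂c)/(p₁c) = p₂/p₁, unchanged. The risk difference is c(p₁ − p₂), which shrinks. For a true 20% v 10%, the normal-approximation power with pooled variance under the null, n = 40 per arm and two-sided 5%, is:

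- c = 100%: difference 0.10, power 24%
- c = 70%: difference 0.07, power 17%
- c = 50%: difference 0.05, power 13%

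**4. Unequal capture with no true effect.** The spurious risk ratio is c(intervention)/c(control).

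- 90% v 70%: 1.29; reversed, 0.78
- 90% v 50%: 1.80; reversed, 0.56

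At p = 15%, 90% v 70% means 13.5% v 10.5%, or 5.4 v 4.2 patients among 40: about one event.

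**5. Window.** A 90-day limit loses nothing against a 90-day endpoint. Against 6 months, with an assumed constant hazard, the 180-day rate is 1 − (1 − p)²: 19%, 28% and 36% for p = 10%, 15% and 20%. The 90-day window then covers 53%, 54% and 56% of patients readmitted by 180 days. What does not fit is the pairing of a 90-day endpoint with a single tick at 6 months, with nothing said about how the two relate.

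**The case against.** The strongest reply is that most of this is a matter of choice for a secondary outcome in a trial of 80 patients. Ninety days roughly matches the post-discharge intervention of about 3 months, and the objective sets no horizon. Patients enrol on admission while the 90 days run from discharge. If 3 months is counted from baseline, that visit falls before the window closes, and 6 months is the first scheduled visit that covers all of it. Section 7 already suggests that follow-up studies use health insurance data to track hospitalisation. Power is low under any definition. This largely stands: the window itself is defensible, and Table 2 needs a clarifying line rather than a new endpoint.

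Two stronger readings are tempting, and the documents do not support them.

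- A reader might infer that the single-hospital rule, the elective category and the 90-day limit all make the outcome undercount. Only the hospital rule can do so. Elective surgery adds events, and the window defines the endpoint.
- A reader might infer that daily messages and weekly calls bring intervention patients back to this hospital more often, biasing the result against the intervention. No passage says that capture differs by arm. The stated purpose of the calls is technical difficulties and negative emotions, not admissions. Questionnaires are given by telephone to both arms after discharge (section 3), and section 6.1 keeps survey times essentially the same. If arm-specific contact does change where patients seek care, the direction is unknown.

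None of this answers the contradiction over scheduled admissions or the recording of outside events as non-events. A suggestion for later studies does not repair this trial.

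**Conclusion.** The point holds as a correction that should be made. The text alone establishes that the numerator is contradictory for scheduled admissions, that admissions and recurrent strokes treated elsewhere are scored as non-events, that the 90-day window is not clearly tied to the 6-month tick in Table 2, and that sections 5.9 and 3 disagree on whether the outcome is primary.

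The size rests on assumption, since the documents give neither a readmission rate nor the share treated elsewhere. On the ranges used, 10% to 50% of events are lost, which is 0.4 to 4 patients per arm. With equal capture the risk ratio is unbiased and only the risk difference and power fall. Bias between arms, in either direction, is a possibility that the present definition does not guard against; it is not a demonstrated fault.

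**What to change.** In section 5.9:

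1. Make the definition, the categories and the numerator agree on scheduled admissions. One consistent version is unscheduled admissions only, with elective surgery removed from the categories and the numerator reworded to match.
2. Count admissions to any hospital. Ask the same question in both arms at the existing 3- and 6-month contacts, record the date of each admission so that the window can be applied, and check against the study hospital's records. Do not use the weekly intervention-arm calls as a source, because that would create unequal ascertainment.
3. State the window and align Table 2 with it: keep 90 days from discharge and, if wanted, add 6 months.
4. Label the outcome secondary, as in section 3. Report proportions by arm with 95% confidence intervals and treat the cause categories as descriptive.

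The cost is one question at contacts that already exist and a reworded definition. The downside is that admissions elsewhere rest on patient report unless a discharge summary is provided.

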In the early stage of IS, intravenous thrombolysis (IVT) is an effective treatment to restore cerebral blood flow and improve neurological function, but it cannot prevent cerebral atherosclerosis or eliminate the risk of recurrence. Some patients still have high rates of disability and recurrence after thrombolysis due to insufficient self-management and treatment compliance (7). Therefore, the implementation of secondary prevention measures is essential to reduce the recurrence rate and improve the prognosis. Secondary prevention targets patients who have had a stroke and aims to reduce the risk of recurrence and improve prognosis (8, 9). In the United States, approximately 700,000 ischemic strokes occur each year, a quarter of which are recurrent strokes, and the risk of death in patients with recurrent strokes is twice as high as that in patients with first-time strokes (10–12). Patients who have had a stroke and TIA have a 40% probability of having another stroke within 5 years and are at high risk for recurrent stroke (13). Most risk factors (e.g., hypertension, diabetes mellitus, hyperlipidemia, etc.) are preventable and controllable, so early secondary prevention is of great significance in improving prognosis (14). Countries have adopted a series of secondary prevention measures, including vascular risk factor management (e.g., antihypertensive, hypoglycemic, and lipid-lowering treatments) (15–19), and lifestyle interventions (e.g., Mediterranean diet, regular exercise, and smoking cessation) (20–22), which are effective in reducing recurrence rates and improving the quality of life of patients.

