### Study participants

2.3

IS patients admitted to Linyi Central Hospital in Shandong Province between June and December 2025 were selected as participants for this study. Eligibility was verified through a two-step process. First, trained staff screened electronic medical records of consecutive ischemic stroke patients. Second, a board-certified neurologist confirmed eligibility through a clinical assessment. Informed consent was obtained only after this verification was complete. Upon admission, patients will complete trial enrolment and sign a study informed consent form via face-to-face, followed by initiation of the 3-month intervention. Although participants are not recruited or initiating the intervention simultaneously, they will all follow the same intervention cycle.

To minimise the risk of cross-group contamination, we implemented stringent control measures across three dimensions: physical, personnel, and procedural. Physically, we allocated distinct follow-up times and consultation rooms for each group, with intervention materials kept under lock and key. Personnel-wise, all staff underwent standardised training, were explicitly prohibited from mentioning intervention details to the control group, and were provided with standardised response scripts. Procedurally, we implemented clear role-based segregation, advised patients at enrolment to avoid cross-group communication, and ensured effective execution of all isolation protocols through regular monitoring.

The study has been approved by the Ethics Committee of Linyi Central Hospital in Shandong Province (LCH-LW-2025031) and registration of the study protocol has been completed with the China Clinical Trial Registry (registration number: ChiCTR2500101457).

Inclusion criteria:

Meet the diagnostic criteria for first-episode ischaemic stroke (62);Age 18 years and above;Be able to operate smartphones and social media applications such as WeChat;Patients or family members signing an informed consent form.

Exclusion criteria:

Patients with cerebral haemorrhage after intravenous thrombolytic therapy;Patients with indications for mechanical thrombolysis by cerebral angiography (CTA) or other imaging tests (63, 64);Patients with severe mental illness, impaired consciousness, and inability to communicate effectively;Patients with severe gastrointestinal bleeding or serious cardiac, hepatic, or renal insufficiency;Patients with cancer or haemorrhagic disease.

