### Statistical analysis

5.10

All participants will be analyzed in the group to which they were randomly assigned, regardless of their adherence to the intervention or whether they completed the study. For participants who are lost to follow-up, we will use multiple imputation to handle missing outcome data, under the assumption that data are missing at random. This approach minimises bias and preserves the benefits of randomization. Data will be entered using Excel and statistically analysed using SPSS27.0 software. The data of count data were expressed as frequency and rate; the data of measurement data conforming to normal distribution were described as mean ± standard deviation, and those not conforming to normal distribution were expressed as median (M) and quartile (P25, P75). Count data were analysed using the chi-square test to analyse the differences between the two groups. Prior to inter-group comparisons, univariate analyses were conducted: independent samples t-tests or one-way ANOVA were employed for data conforming to a normal distribution, while the Mann–Whitney U test or Kruskal-Wallis H test was utilized for non-normally distributed data. Paired t-test was used for intra-group comparisons, and repeated-measures ANOVA was used to evaluate the trend of changes in each index, with *p* < 0.05 as the test level.

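### Stroke recurrence is counted only through readmission among discharged patients and death is not an outcome, so fatal and in-hospital recurrences after randomisation can go uncounted

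*Protocol article*

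**What the plan says.** The objectives at the end of the Introduction include an aim to "track the reduction in the risk of relapse and readmission". Section 5.9 is the only place that says how either is measured.

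- **Event.** A readmission is "any unscheduled admission to our hospital within 90 days of the index stroke discharge".
- **Rate.** The all-cause rate is "calculated as the total number of patients readmitted for any reason divided by the total number of discharged patients".
- **Recurrence.** Section 5.9 states that "all readmissions were systematically reviewed and classified into the following predefined categories", and stroke recurrence is the first of these. It adds: "Secondary outcomes included the readmission rates for each specific category listed above, particularly the rate of stroke recurrence". Recurrence is therefore itself a readmission rate.
- **Death.** It does not appear among the outcomes in section 3, in Table 2 or in section 5.9.
- **Start of trial time.** Section 2.3 says: "Upon admission, patients will complete trial enrolment and sign a study informed consent form via face-to-face, followed by initiation of the 3-month intervention". Section 2.5 places the first session within 48 h of admission and the second shortly before discharge.
- **Analysis set.** Section 5.10 says: "All participants will be analyzed in the group to which they were randomly assigned". This holds whether or not they completed the study.

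**The concern.** The objective concerns relapse, but the measure sees a relapse only if the patient is first discharged and then readmitted to the trial hospital within 90 days. Two kinds of recurrence after randomisation fall outside that: one that kills without a readmission, and one that occurs on the ward before the index discharge. The first is the most severe form of the event that the trial hopes to reduce. The Introduction notes that "the risk of death in patients with recurrent strokes is twice as high as that in patients with first-time strokes". That is background rather than a rate for this sample, but it shows why fatal recurrences should not be left out by definition.

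Dividing by discharged patients also restricts the denominator by something that happens after randomisation. If any randomised patient dies before discharge, the rate no longer compares the groups as randomised.

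**Working it through.** The plan gives no expected readmission, recurrence or death rate, so there is no figure to reproduce. The check applies the stated rule to the possible patient histories and then shows the scale on assumed counts.

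**Step 1: classify patients under section 5.9.** The section gives a denominator only for the all-cause rate; I take the category rates to share it.

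| History after randomisation | Numerator | Denominator | Result |
|---|---|---|---|
| Recurrence after discharge, readmitted to the trial hospital within 90 days, fatal or not | yes | yes | counted |
| Discharged, dies of a recurrence without readmission | no | yes | event-free |
| Non-fatal recurrence during the index stay, then discharged | no | yes | event-free for that recurrence |
| Dies before discharge | no | no | drops out |

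Rows 3 and 4 lie within trial time, because enrolment and the first two intervention sessions come before discharge (sections 2.3 and 2.5).

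**Step 2: formulas.** Inputs are 40 randomised per arm (section 2.4) and three assumed counts: r patients readmitted, a deaths after discharge without readmission, and b deaths before discharge.

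- Stated rule: r / (40 − b)
- Readmission or death over all randomised: (r + a + b) / 40

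**Step 3: results for r = 4.**

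| a | b | Stated rule | Readmission or death, all randomised |
|---|---|---|---|
| 0 | 0 | 4/40 = 10.0% | 4/40 = 10.0% |
| 1 | 0 | 4/40 = 10.0% | 5/40 = 12.5% |
| 0 | 1 | 4/39 = 10.3% | 5/40 = 12.5% |
| 2 | 0 | 4/40 = 10.0% | 6/40 = 15.0% |
| 2 | 1 | 4/39 = 10.3% | 7/40 = 17.5% |

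Over r = 2 to 6, a = 0 to 3 and b = 0 to 2, the stated rate runs from 5.0% to 15.8% and the alternative from 5.0% to 27.5%.

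**Step 4: direction.** A death at home adds nothing to the stated rate, which then lies 1/40 = 2.5 points below a rate that counts it. A death before discharge shrinks the denominator and moves the stated rate up, here by 0.3 points.

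**Step 5: effect on a comparison.** Suppose each arm has 40 discharged patients and 4 recurrences after discharge, with no other readmissions. If all 4 are readmitted in one arm, its rate is 4/40 = 10.0%. If 3 are readmitted in the other and 1 dies at home, its rate is 3/40 = 7.5%. The arms appear to differ by 2.5 points with equal numbers of recurrences, and the arm with the fatal one looks better.

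**The case against.** Readmission per discharged patient, timed from discharge, is a coherent measure, and section 5.9 presents it as a post-discharge outcome. A patient cannot be readmitted before being discharged, and timing readmission from randomisation would make time at risk depend on length of stay. This stands, and it is why 90-day readmission from discharge can be kept. It does not help recurrence, which can occur from randomisation onward and has no other measure in the article.

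The conflict with the as-randomised analysis is conditional: it arises only if someone dies before discharge. That also stands. How deaths are handled in the analysis may be set out in a fuller document, but the point here does not rest on a missing rule. The numerator and denominator are printed, and they produce the classification above.

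A reader might infer that a death always lowers its arm's rate, so that an arm with more deaths must look better. The formula does not support this. A pre-discharge death raises the rate slightly, and a death at home lowers it only relative to a counted event.

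A reader might also infer that deaths are lost to the trial, or that the endpoint fails as a safety measure. The article never gives readmission that role. Section 6.10 has all serious adverse events recorded and reported within 24 h, and section 6.9 provides an independent data monitoring committee. Those records do not, however, enter the readmission or recurrence rate.

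Finally, the outcome is a minor one. Section 3 lists readmission last among the secondary clinical indicators, although section 5.9 uses the word primary for it. The entry criteria exclude several high-risk groups, so few deaths are expected.

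**Conclusion.** The point holds as a defect in the definition of the recurrence outcome. Applied as written, section 5.9 scores a fatal recurrence without readmission as event-free, does not count a non-fatal recurrence on the ward, and removes patients who die before discharge. This weakens the relapse objective and departs from section 5.10 whenever a pre-discharge death occurs.

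Its size in this trial is unknown, because the article gives no event rates, and is probably small. Each uncounted post-discharge death is worth 2.5 points in an arm of 40, and each pre-discharge death moves the stated rate up by a fraction of a point. The net direction is not fixed. The illustrations rest on assumed counts and on all 40 patients per arm being recruited. The reason to act is that the misclassified events are the most serious ones and the correction is cheap.

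**What to change.** - **Recurrence.** In section 5.9, define it separately from readmission. Count it from randomisation to a fixed follow-up time over all randomised patients, whether fatal or not, in hospital or after discharge, and at whatever hospital it is treated.
- **Readmission.** Keep 90-day readmission from discharge if wanted. Beside it, report readmission or death from any cause with all randomised patients as the denominator, and state its time window.
- **Deaths.** List them by arm and cause, using a vital-status field at the planned 3- and 6-month contacts.

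The cost is protocol wording and one data field, with no added visit. The downsides are that the reported event rate may be slightly less favourable and that the added endpoint is a composite, so its components should be shown separately.
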